### The Study Process and Data Collection

The flowchart of the study process is presented in Figure 1.

At baseline, patient history, including age, gender, body mass index, smoking status, comorbidities, primary diagnosis, and ASA grade, will be collected. The patient questionnaires and VAS scale will be administered at baseline, POD 1, and POD 3 to patients with no knowledge of their treatment allocation. On arrival at the anesthetic room and during the procedure, the temperature will be measured using a urinary temperature probe.

**Figure 1 figure1:**
[figure not shown]
The study process with recruitment, data collection, follow-up, and final analysis.

Patients’ complications (including surgical site infections) will be reported at POD 1, POD 3, upon discharge and at POD 30. All resource use will be routinely recorded at each time point.

### Data Analysis

The statistical analysis plan will be followed for all clinical and economic analyses. Intention-to-treat analysis, the primary analysis method, will take into account minimization factors and sites. Whenever possible, standard errors, confidence intervals, and *P* values will be reported for outcomes.

Assuming a normal distribution of the data, the change in QoR-40 between groups will be analyzed with ANCOVA (analysis of covariance) while controlling for the baseline. The logistic regression for incidence rates will be used to compare the incidence of hypothermia between groups. ANCOVA will be used to compare the duration and depth of hypothermia and the Comprehensive Complication Index scores between groups. The incidence of surgical site infections, length of stay and procedure, and readmission rates will be summarized with descriptive statistics.

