**Objective:**

The aim is to determine if insufflation with warmed, humidified CO_2_ using the HumiGard device, alongside standard perioperative warming techniques, can improve patient recovery, including pain, surgical site infections, complications, and the use of analgesia compared with standard care alone.

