### Clinical Outcomes

The primary outcome measure is the change in patient-reported QoR-40 (quality of recovery) scores from baseline to postoperative day 1 (POD 1).

The QoR-40 is a widely used and validated questionnaire that provides a patient-reported measure of recovery following surgery and anesthesia [11]. The questionnaire includes 40 items separated across five dimensions: patient support, comfort, emotions, physical independence, and pain. The QoR-40 is a reliable and valid tool for assessment of the quality of recovery in patients. It has very high acceptability among patients and is highly sensitive to any clinical changes [12].

The secondary outcomes for this study are:

Change in QoR-40 scores from baseline to POD 3.Change in patient-recorded pain scores from baseline to POD 1 and POD 3 using a visual analog scale (VAS). The score will range from 0 to 100.The incidence of hypothermia during the surgery (body temperature drop to 36°C during the procedure as recorded in the patient’s notes).Duration and depth (overall minimum temperature) of hypothermia.The rate of postoperative complications recorded at POD 1, POD 3, at discharge, and at POD 30. The severity will be assessed with the Clavien-Dindo scale, which is widely used for grading the severity of surgical complications in patients [13]. The Comprehensive Complication Index will be used later to create a composite score (0-100) for each patient [14].The incidence of site surgical infections within the first 30 days postsurgery.Length of stay in hospital from procedure to discharge (or until medically fit to discharge).Resource use outcomes, including analgesia (type and dose), use of strategies to maintain perioperative normothermia (eg, warming blanket, fluid warmer), time to discharge, length of procedure, length of recovery time, and readmission to hospital.Cost-effectiveness analysis of the HumiGard device compared with standard care.

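### Surgical site infection is named in the comparative objective but assigned descriptive statistics, so the plan does not commit to a between-arm estimate of it

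*Protocol article*

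**What the plan says.** The Objective in the Abstract asks whether the device, added to standard warming, "can improve patient recovery, including pain, surgical site infections, complications, and the use of analgesia compared with standard care alone". That is a question about a difference between arms, and infection is one of the four items it names. Clinical Outcomes lists infection within 30 days as a secondary outcome in its own right.

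The Data Analysis section contains four statements that bear on it:

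- On infection itself: "The incidence of surgical site infections, length of stay and procedure, and readmission rates will be summarized with descriptive statistics".
- On reporting in general: "Whenever possible, standard errors, confidence intervals, and *P* values will be reported for outcomes".
- On another binary secondary outcome: "The logistic regression for incidence rates will be used to compare the incidence of hypothermia between groups".
- On the governing document: "The statistical analysis plan will be followed for all clinical and economic analyses".

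The section also assigns ANCOVA to the Comprehensive Complication Index, and says the intention-to-treat analysis allows for the minimization factors and for site. The Economic Evaluation section uses infection rates as inputs to its decision tree.

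**The concern.** A method has been chosen for infection, and it does not match the question asked. The article is not silent here, so this is not something simply left to the analysis plan. An analysis plan that followed the descriptive sentence literally would contain no infection comparison. No reason is given for treating infection differently from hypothermia, although both are incidences compared between two randomized arms.

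What is at stake is how the result will be read. Two percentages printed side by side invite comparison whether or not the authors intend one. In a trial of this size a gap of several percentage points can easily arise by chance, and without an interval it could be taken as benefit or harm. Infection also enters the cost model, where the planned probabilistic sensitivity analysis needs a measure of uncertainty around it.

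**Working it through.** **Is there a figure to reproduce?** No. The protocol gives no infection rate, target difference or power for infection. Its only sample size is for the QoR-40. What can be computed is how precise an infection comparison would be, under assumed rates.

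**Inputs**

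- Patients per arm: 116 (required) and 129 (recruited), from Sample Size Estimation. The 10% loss allowed there is for the QoR-40 at 24 hours, and no loss is stated for infection at 30 days. So 129 represents no loss, and 129 × 0.90 ≈ 116 represents a 10% loss.
- Infection rates: 10% and 20%, assumed.
- Two-sided 5% level, assumed; the protocol gives 5% without stating sidedness.

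**Interval half-width when both arms share rate p:** 1.96 × √(2p(1−p)/n)

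| p | n = 116 | n = 129 |
|---|---|---|
| 10% | 1.96 × √(0.18/116) = 7.7 points | 1.96 × √(0.18/129) = 7.3 points |
| 20% | 1.96 × √(0.32/116) = 10.3 points | 1.96 × √(0.32/129) = 9.8 points |

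So at a true rate of 10% in both arms, observed gaps of up to about 7 to 8 points in either direction are within ordinary chance variation.

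**Half-width if the rate is halved:** 1.96 × √(p₁(1−p₁)/n + p₂(1−p₂)/n)

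- 10% against 5%: 6.7 points (n = 116), 6.4 points (n = 129), around a true difference of 5.
- 20% against 10%: 9.1 points (n = 116), 8.6 points (n = 129), around a true difference of 10.

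**Power for a halving:** Φ([|p₁−p₂| − 1.96√(2p̄(1−p̄)/n)] / √([p₁(1−p₁)+p₂(1−p₂)]/n)), with p̄ the mean of the two rates. For 20% against 10% at n = 116 this is Φ((0.100 − 0.0919)/0.0464) = Φ(0.17) = 57%.

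| Rates | n = 116 | n = 129 | n per arm for 80% power |
|---|---|---|---|
| 10% vs 5% | 30% | 33% | 435 |
| 20% vs 10% | 57% | 61% | 199 |

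**Can the model be adjusted?** At 10% in both arms, 2 × 129 × 0.10 ≈ 26 events are expected. A model with treatment (1 term), ASA grade as one linear term (1), gender (1), benign or malignant procedure (1) and at least four sites (3 or more) has at least 7 terms, or 26/7 ≈ 3.7 events per term. At 20% the figure is 52/7 ≈ 7.4. Full adjustment may not be supportable, so an unadjusted fallback is needed.

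**The case against.** The best defence is that the general reporting rule already covers infection. An interval for a difference in proportions is always possible, so the rule could be read as promising one, and the analysis plan, which is not shown, may say so. This defeats the stronger reading that the trial cannot answer its infection question, or that readers will get percentages with no uncertainty at all; the document does not establish either. It does not remove the conflict, because the specific sentence about infection points the other way and the two need reconciling.

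A second defence is that infections are recorded among the complications, and the Comprehensive Complication Index is compared by ANCOVA. A reader might infer that the Discussion's expectation of fewer complications and quicker recovery rests on description alone. It does not, since both the index and the QoR-40 have between-group models. But a single composite score per patient yields no effect on infection as such.

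A third is that low power argues against a formal test. It does argue against a confirmatory claim. It does not argue against an estimate with an interval, which is how low precision is made visible.

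A reader might also extend the point to length of stay and readmission, which share the descriptive sentence. The Objective does not name them, so describing them contradicts nothing in it. Nor would a chance difference in infection pass unchecked into the cost model: that analysis is conditional on clinical effectiveness and includes deterministic, probabilistic and scenario analyses.

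**Conclusion.** The point holds for surgical site infection only. The Objective poses a between-arm question about it, and Data Analysis assigns it description, against that section's own reporting rule and its handling of hypothermia. The plan does not commit to a between-arm estimate; it would be too much to say that it rules one out.

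The primary analysis is unaffected. At 116 to 129 per arm the interval would reach about 7 to 10 points either side, with power for a halving of roughly 30–33% from 10% and 57–61% from 20%. These figures rest on infection rates assumed here, on a two-sided 5% level, and on 30-day follow-up between complete and 90%.

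**What to change.** In Data Analysis, remove infection from the descriptive sentence and add text such as: *Surgical site infection within 30 days will be compared between arms by logistic regression, adjusted for the minimization factors and site where event numbers allow and otherwise unadjusted. Results will be given as a risk difference and an odds ratio, each with a 95% confidence interval. This is a secondary estimate that the trial is not powered to test.* The rule for falling back to the unadjusted model should be fixed before allocation is revealed.

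Length of stay, procedure length and readmission can stay as they are for the purposes of this point.

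The cost is a few lines of text and one further analysis of data already being collected. The drawback is that the interval will be wide and may well be compatible with both benefit and harm, which the report will have to say plainly.

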### Economic Evaluation

If the intervention is deemed clinically effective, we aim to perform a cost-consequence analysis. The analysis will consider the costs and resource consequences resulting from, or associated with, the use of the HumiGard device plus standard care compared with standard care alone. The model will be produced in MS Excel.

To fully evaluate the impact of the HumiGard device on the current health care system within the United Kingdom, we aim to design the model from an NHS perspective and have a 1-year time horizon. We aim to perform a within-trial analysis with a decision tree that incorporates the rates of complications such as surgical site infections. We will apply the standard discount rate of 3.5%, and the costs of complications and admission rates will be based on NHS reference costs. Differences in staff and bed costs, associated with factors such as length of stay will be included. The cost of analgesia and resource use needed during surgery to maintain normothermia will be incorporated into the cost model.

We will carry out a scenario analysis to validate the model, compare it with other published evidence, and test the impact of changes within the model structure on the base case results. The impact of other published and clinical data will be tested. Deterministic and probabilistic sensitivity analysis will also be performed.

## Results

### Service Evaluation

The preparation of the study protocol was preceded by a small-scale service evaluation carried out in the University Hospital of Wales in Cardiff, United Kingdom. The team investigated the ability and willingness of patients to complete QoR questionnaires before and after laparoscopic colorectal surgery, potential recruitment rates, and informed the design of the data capture tools and database. The study was deemed as nonresearch and approved by Cardiff & Vale University Health Board.

During one month of data collection, seven eligible patients were asked to fill in presurgery (on the day of surgery) and postsurgery (POD 1) questionnaires. The baseline characteristics, intraoperative data, and questionnaire-related completion rates are presented in Table 1. All seven patients filled in the QoR-40 questionnaires at both time points. All patients fully completed the preoperative QoR-40 questionnaire and six of seven patients fully completed all the domains from the postoperative questionnaire (one answer was missing in one of the domains). Six of seven patients completed the preoperative VAS pain question; all patients completed the postoperative VAS pain question.

Statistical analysis of the data collected was not performed due to the low number of patients.

The data obtained from the service evaluation provided “proof of principle” evidence that patients in this setting are amenable to completing the QoR-40.

**Table 1 table1:** Baseline characteristics and intra- and postoperative patient information (N=7).

Characteristic			Participants
**Baseline data**			
	Age (years), mean (range)		50 (19-70)
	**Sex, n (%)**		
		Female	5 (71)
		Male	2 (29)
	**ASA^a^ grade, n (%)**		
		1	1 (14)
		2	4 (57)
		3	2 (29)
	**Type of surgery, n (%)**		
		Laparoscopic elective colectomy	7 (100)
		Open surgery	0 (0)
**Intraoperative data**			
	**Temperature at arrival to theater, n (%)**		
		<36°C	2 (29)
		>36°C	3 (43)
		Unknown	2 (29)
	**Temperature at the end of surgery, n (%)**		
		<36°C	2 (29)
		>36°C	5 (71)
		No change during surgery	2 (29)
		Higher (range 0.3°C-1°C) than at arrival	3 (43)
	Complications (during hospital stay), n		0
	Surgery time (hours), mean (range)		3.33 (1.58-4.17)
**Postsurgery admission**			
	Postanesthesia care unit, n (%)		1 (14)
	Ward, n (%)		6 (86)
	Hospital stay (days), mean (range)		8 (6-15)
**QoR-40^b^ completion rates, n (%)**			
	Fully completed preoperative QoR-40 questionnaires		7 (100)
	Fully completed postoperative QoR-40 questionnaires		6 (86)
**VAS^c^ pain score completion rates**			
	Fully completed preoperative VAS pain score		6 (86)
	Fully completed postoperative VAS pain score		7 (100)

^a^ASA: American Society of Anesthesiologists.

^b^QoR-40: quality of recovery questionnaire.

^c^VAS: visual analog scale.

### Feasibility Study

Following the service evaluation and the preparation of this manuscript, the team received an unrestricted grant for a small feasibility study from Fisher & Paykel Healthcare, the manufacturer of the HumiGard device. The study will use a similar protocol to that described in this publication; however, only 40 patients will be randomized to study arms. The feasibility study will be carried out in the University Hospital of Wales in Cardiff, United Kingdom, and the results will support the funding application for the full-scale RCT described previously.

## Discussion

Systematic reviews [7,8] identified significant weaknesses in the current evidence base for whether using warmed and humidified insufflation gas improves postoperative outcomes for patients. This study is designed to provide information relating to the use of the HumiGard device that is not presently available in the published literature.

Most studies identified did not have the sufficient number of patients required (>100 participants) to show any difference between the comparators. To detect a change in the primary outcome, our sample size will be appropriately powered, and the number of patients will be at least double the size of the cohorts in the published studies. Moreover, the study has a robust, multicenter design with blinding of allocation (patient and outcome assessor).

The control arm will adequately reflect current practice within the United Kingdom and is comparable to the standard practice in other countries. Patients undergoing colorectal surgery have a relatively high risk of developing hypothermia and suffering from postoperative complications due to the length and nature of the procedure as well as existing comorbidities. The inclusion of a control group will help to detect differences between the two arms of the study, if they exist.

More importantly, the study is focused on patient-reported QoR, which will provide an in-depth assessment of patients’ physical recovery, level of emotional stress, and discomfort. It is likely that the QoR-40 will be more sensitive to postsurgery changes in patients’ outcomes than a generic quality-of-life tool because it is focused directly on the time following surgery. Moreover, the “comfort”’ section includes questions regarding shivering and “feeling too cold,” which are relevant to hypothermia. Based on the short service evaluation conducted in University Hospital of Wales in Cardiff, patients are willing to fill in the QoR-40 questionnaires. Thus, QoR-40 is an appropriate tool to use during the proposed RCT.

The clinical trial will provide high-quality evidence necessary to support recommendations about whether HumiGard should be routinely adopted in the hospital setting for patients undergoing surgery. If HumiGard is shown to be effective, patients will benefit from fewer complications and quicker recovery on adoption of this technology. However, if the device is no better than standard care, the health service can avoid unnecessary investments.

One of the major limitations of this or any other medical device study is the short life span of the equipment involved. Medical devices may be expected to provide a long service life; however, it is the manufacturer’s decision when a device is modified or replaced by another model. Unfortunately, the data from clinical trials and other studies are not always transferable, and new evidence must be collected to assess the clinical and cost-effectiveness of devices in which significant modifications have been made.

## Abbreviations

ASA: American Society of Anesthesiologists
NHS: National Health Service
NICE: National Institute for Health and Care Excellence
POD: postoperative day
QoR: quality of recovery
RCT: randomized controlled trial
VAS: visual analog scale
